### Knowledge brokers

This trial will evaluate a complex intervention involving on-site embedded pharmacists working as knowledge brokers at each aged care provider organisation. Each aged care provider organisation will recruit and employ or contract their own knowledge brokers. The Project Management Team will engage with each aged care provider organisation to help identify suitable knowledge brokers if required. Knowledge brokers will be identified through an expression of interest process via direct approaches to the aged care provider’s existing pharmacy service provider, direct approach to known professional contacts of the Project Management Team or aged care provider organisation or via local advertisements.

Pharmacists will be eligible to be a knowledge broker if they:Hold general pharmacist registration with the Australian Health Practitioner Regulation Agency.Are willing and available to commit to undertake the role for 12 months, including completing training and specific tasks of the trial.Are willing and able to complete all relevant aged care provider organisation induction and occupation, health and safety training requirements and be contracted or employed to work with each aged care provider.

It will be desirable for the knowledge brokers to have prior aged care experience and accreditation to complete medication management reviews (MMRs), but this will not be a requirement [28]. Potential knowledge brokers will be provided with an explanatory statement, and written informed consent will be sought from the knowledge brokers. Knowledge brokers will be trained to support delivery of the implementation strategies by undergoing a training programme over a 4–5-week period prior to trial commencement. The training program consists of the following:3 × 1.5-h online workshops on knowledge translation delivered by implementation science experts. The workshops include one self-paced and two interactive modules that cover evidence implementation, stakeholder engagement, driving meaningful change and the integrated-Promoting Action on Research Implementation in Health Services (i-PARIHS) framework. These modules have been developed for the purpose of the trial and were informed by the foundational activities described earlier.A 1.5-h online webinar on the EMBRACE trial design and the intervention and guidance on how to deliver the implementation strategies delivered by the Project Management Team.A 1.5-h webinar on the Guidelines delivered by the Project Management Team [12]Residential Aged Care Pharmacist Foundation Training Program developed and delivered by the Pharmaceutical Society of Australia [29]. This 9-h programme involves four residential aged care online modules, nine video lectures on aged care clinical topics, three optional modules dedicated to QUM and two optional modules on health literacy and digital literacy.

### Intervention

All three levels of implementation strategies will be delivered simultaneously throughout the 12-month intervention period at the RACF-level. Each level of implementation strategy includes the activities of the previous level (Table 1). Education resources will be provided to support knowledge brokers to deliver level 1 and level 2 implementation strategies. Level 3 implementation strategies will be customised to each RACF based on ongoing local needs assessments conducted by the knowledge broker.

#### Level 1: Distribution of the Guidelines and supporting materials

The level 1 strategy will involve passive distribution of the Guidelines and supporting materials in both hard copy and electronically to the RACF, including on-site staff (e.g. nurses and aged care workers) and visiting healthcare professionals (e.g. medical practitioners and allied health). Materials will be distributed by the on-site aged care pharmacist at baseline as well as on request. Distributed materials will include the Guidelines, a companion guide, medication factsheets on the allocated medication context (antipsychotics, benzodiazepines or antidepressants) and a curated inventory of existing resources. All these materials will also be publicly available via MAGICapp, an online platform for publication of guidelines and evidence summaries [12]. The level 1 resources will be standardised, and no tailoring of these resources will be undertaken by the Project Management Team. The level 1 strategy is consistent with standard implementation of most clinical practice guidelines in Australian RACFs.

#### Level 2: Pharmacist-led QUM education activities

The level 2 strategy will involve provision of QUM services and distribution of the Guidelines and supporting materials. QUM services are Australian government-funded pharmacist-led group education activities [30]. The QUM service used in this trial will be developed to align with the Pharmaceutical Society of Australia Guidelines for QUM services and the Guidelines [30]. The QUM service will involve a face-to-face, online or pre-recorded group education activity delivered by an on-site aged care pharmacist, delivered to RACF registered nurses and enrolled nurses and aged care workers directly employed by the aged care provider organisation. Each QUM session will run for up to 70 min. The pharmacist will deliver a QUM service once per quarter, with a total of four QUM services delivered over the 12 months. The four sessions will cover the Guidelines, initiation, adverse events and monitoring and discontinuation relevant to the RACFs’ allocated medication context (Table 2).

**Table 2 Tab2:** Overview of QUM service to RACFs

		**Overview**	**Key take-home messages**
**Guideline introduction**		Introduction to the Guidelines, including the companion guide, medication factsheets and curated inventory of existing resources	Understand the background of the Guidelines, terminology used within the Guidelines and scope of the Guidelines
**Education activity**	Initiation	Each education activity will begin with a brief overview on the use of the psychotropic medication in people living with dementia and changed behaviours Attendees will work through a case study in small groups. Attendees will present their case study answers, and the facilitator will support group discussion. The facilitator will end the education activity with a brief conclusion of the key take-home messages Each component of the education activity will include interactive components to promote group discussion	The *initiation* education activity takes staff through the risks and benefits of the psychotropic medication for people living with dementia. It teaches nurses and aged care staff the steps they should take prior to considering initiation of the psychotropic medication
	Adverse events and monitoring		The *adverse events and monitoring* education activity reviews some key adverse events of the psychotropic medication and teaches nurses and aged care staff monitoring requirements for the psychotropic medication
	Discontinuation		The *discontinuation* education activity teaches nurses and aged care staff when discontinuation should be considered for the psychotropic medication and monitoring requirements during the discontinuation process

Abbreviations: *RACF*, residential aged care facility; *QUM*, quality use of medicine

The Project Management Team will provide education resources to assist in leading the QUM service, including facilitator notes, presentation slides and a sample presentation script. The QUM service resources have been piloted with a Queensland-based regional aged care provider organisation, not otherwise participating in the trial, to test the feasibility of the resources. The level 2 resources will be standardised, and no local tailoring of materials will be undertaken by the Project Management Team. The level 2 intervention is an example of current best practice in relation to implementation of clinical practice guidelines in Australian RACFs.

#### Level 3: Knowledge broker service

The level 3 strategy will involve the on-site knowledge broker who will develop and lead local action plans, as well as provision of QUM services and distribution of the Guideline materials. The knowledge brokers will be employed at the aged care provider organisation level and will work across each participating RACF for that organisation. The knowledge broker will collaborate with the aged care provider organisation’s Medication Advisory Committee (MAC; a multidisciplinary group of healthcare professionals, carers and residents who implement and evaluate medication management policies and procedures [31]) to develop and implement RACF-specific local action plans underpinned by the i-PARIHS framework [32]. Local action plans will be data driven and informed by the trial indicators, iteratively reviewed and updated each quarter (Table 3). The knowledge broker will be an ‘intermediary’ to facilitate knowledge translation by acting as a knowledge manager, capacity builder and linkage agent [16, 21].Knowledge manager activities may include embedding and application of Guideline knowledge into local contexts, policies and procedures, assessing barriers and enablers to Guideline implementation in the local context and preparing a local action plan.Capacity builder activities may include developing staff knowledge and skills to facilitate and enable Guideline-concordant decision-making, coordinating education relevant to Guideline implementation and conducting audits and providing feedback using indicators of guideline concordance to evaluate implementation initiatives.Linkage agent activities may include facilitating collaboration between medical practitioners, nurses and aged care workers, residents and their families, being a conduit between the Project Management Team and the RACF employed staff and visiting team members, and communicating with other knowledge brokers in the trial.

**Table 3 Tab3:** Knowledge broker study activity requirements for level 3 intervention

Time point	Reporting and study activity requirement
Baseline	*Training and orientation*: Knowledge broker will participate in training and RACF orientation
	*Local action plan*: Knowledge broker will develop local action plan for each RACF and present to RACF management team, Medication Advisory Committee and Project Management Team
	*QUM service*: Delivery of first QUM service according to group allocations
	*Intervention*: Delivery of knowledge broker services as per local action plan
3-month time point	*Local action plan*: Knowledge broker will review and update the local action plan for each RACF (including reflection on successes and challenges in previous quarter) and present to RACF management team, Medication Advisory Committee and Project Management Team
	*QUM service*: Delivery of second QUM service according to group allocations
	*Intervention*: Ongoing delivery of knowledge broker services as per local action plan Support and evaluation: Engagement in semi-structured interviews and focus groups
6-month time point	*Local action plan*: Knowledge broker will review and update the local action plan for each RACF (including reflection on successes and challenges in previous quarter) and present to RACF management team, Medication Advisory Committee and Project Management Team
	*QUM service*: Delivery of third QUM service according to group allocations
	*Intervention*: Ongoing delivery of knowledge broker services as per local action plan *Support and evaluation*: Engagement in semi-structured interviews and focus groups
9-month time point	*Local action plan*: Knowledge broker will review and update the local action plan for each RACF (including reflection on successes and challenges in previous quarter) and present to RACF management team, Medication Advisory Committee and Project Management Team
	*QUM service*: Delivery of fourth and final QUM service according to group allocations
	*Intervention*: Ongoing delivery of knowledge broker services as per local action plan *Support and evaluation*: Engagement in semi-structured interviews and focus groups
12-month time point	*Local action plan*: Knowledge broker will reflect on success and challenges for previous quarter
	*Study close-out*: Semi-structured interviews and focus groups with knowledge brokers

Abbreviations: *RACF*, residential aged care facility; *QUM*, quality use of medicine

Ongoing fidelity of the intervention delivered by the knowledge brokers will be monitored using the discussion boards, local action plans and monthly meetings with the Project Management Team. Meetings will mostly be conducted via video-teleconferencing (e.g. Zoom), with face-to-face meetings organised if needed.

### Data collection

Data collection from the RACFs will occur at baseline and quarterly (3, 6, 9 and 12 months; Table 4). The data collected in this trial will include de-identified data extracted from existing routinely collected data sources within each RACF. Existing data sources will include National Aged Care Mandatory Quality Indicator Program records [33], psychotropic registers [34], prescribing and medication administration records, nursing progress notes, medical records and behaviour support plans. Data will be collected by trained aged care nurses, health or care professionals, employed or contracted by each of the participating aged care provider organisations, who will be blinded to the RACF group allocations. One or more nurses, health or care professionals per participating aged care provider organisation will attend an online training webinar on data collection led by the Project Management Team. Data will be collected and stored on a secure server by Monash University using REDCap™ (Research Electronic Data Capture), a secure web-based software platform designed to support data capture for research studies [35, 36]. Trial data will be stored for a minimum of 15 years after publication of result in accordance with Australian NHMRC and Monash University guidance for medical research involving clinical trials. The final trial dataset will only be accessible to the trial investigators and statistician or epidemiologist.

**Table 4 Tab4:** SPIRIT diagram — schedule of enrolment, intervention, and assessment for the EMBRACE trial

Trial period								Data source
**Time point**	Enrolment	Allocation	Intervention period					
	*-t*	*-t*	0	3	6	9	12	

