### Randomisation and blinding

This trial will involve RACF-level interventions, and individual residents will not be recruited to participate. The unit of randomisation will be RACFs. Once potential availability of specific RACFs is determined by each aged care provider organisation, the RACF manager or an authorised representative of the aged care provider organisation will be provided with a written explanatory statement, and informed consent to participate will be obtained.

RACFs will be matched into blocks of three based on the aged care provider organisation and geographical location. One RACF within each block of three will be randomised to groups A, B, or C and receive three levels of intervention for a combination of implementation strategies and medication contexts (Table 1). Randomisation will be performed by an independent epidemiologist using a computerised random number generator within SAS (SAS Institute, Cary, NC, USA).

Following randomisation, each aged care provider organisation leadership team and their knowledge brokers will be notified of group allocations for each participating RACF within their organisation. Due to the nature of the trial, it will not be possible to blind the leadership team or knowledge brokers. Partial disclosure will be implemented for RACF nurses, aged care workers and visiting pharmacist and medical practitioners at each RACF. These clinicians and staff will be aware of the trial objectives and implementation strategies but will be blinded to the RACF group allocation. The availability of the knowledge broker service will be communicated via letters, posters and notice boards. Residents and their families will be made aware of the trial through distribution of notices and posters at each RACF. The primary outcome will be analysed by a blinded statistician or epidemiologist. The Project Management Team will not be blinded to the group allocations.

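### Staff blinding to group contradicts how the strategies are delivered, and blinding of the outcome collectors is asserted without a stated safeguard

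*Protocol article*

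**What the plan says.** Two statements on blinding matter here.

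- Staff. Under Randomisation and blinding, facility nurses, care workers and visiting clinicians "will be aware of the trial objectives and implementation strategies but will be blinded to the RACF group allocation". The article calls this partial disclosure.
- Outcome collectors. Under Data collection, they are trained nurses or other health or care professionals, on the providers' staff or under contract to them, "who will be blinded to the RACF group allocations". The section on RACF Guideline concordance gives these people the task of assessing the indicators in Tables 5 to 7.

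The delivery sections say the following.

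- The Level 2 education sessions are "delivered to RACF registered nurses and enrolled nurses and aged care workers directly employed by the aged care provider organisation".
- Their content is class-specific: "The four sessions will cover the Guidelines, initiation, adverse events and monitoring and discontinuation relevant to the" class allocated to that facility.
- The Intervention section makes the levels cumulative, and Table 1 lists education sessions under Level 3 as well as Level 2.
- Table 3 places sessions at baseline and at 3, 6 and 9 months. The primary outcome is measured at 6 months.

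**The concern.** A facility's group is nothing more than which drug class receives which strategy. People who know the three strategies and sit in the class-specific sessions are being told most of that assignment. If outcome collectors share this knowledge, they can score the primary outcome knowing which class had the knowledge broker.

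The design makes this matter more than usual. Strategy varies by class within each facility, and one collector may score all three classes there. Leniency towards the Level 3 class therefore falls on the contrast that the mixed model estimates. The random intercept for facility removes only what is common to the three classes. Counterbalancing balances class effects across strategies, but this error follows the strategy. The blinded analyst and the central computation of concordance by a third party both act after the indicators have been scored.

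At stake are a trial report that describes blinding the design does not give, and some unmeasured bias in favour of the broker strategy.

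**Working it through.** **Step 1: does what staff see reveal the group?** Inputs: Table 1 and the rule that each level includes the one below it.

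| Group | Level 1 (no sessions) | Level 2 (sessions) | Level 3 (sessions and broker) |
|---|---|---|---|
| A | antidepressants | benzodiazepines | antipsychotics |
| B | antipsychotics | antidepressants | benzodiazepines |
| C | benzodiazepines | antipsychotics | antidepressants |

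This is a 3 × 3 Latin square, so each pairing of class and level occurs in exactly one group. Exactly two classes are taught in each facility: antipsychotics and benzodiazepines in A, antidepressants and benzodiazepines in B, antidepressants and antipsychotics in C. The untaught class is different in each group. Anyone who knows the strategies can see that it is the Level 1 class. With Table 1, which this article prints, the other two levels follow.

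**Step 2: is this known by the primary time point?** Two sessions are scheduled before 6 months. Table 2 lists a general introduction first. If the sessions run in that order (an assumption), the one at 3 months already concerns initiation of a named class.

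**Step 3: can collectors be in that audience?** The sessions are for nurses and care workers directly employed by the provider. Collectors are nurses or other professionals employed or contracted by the provider. The two pools overlap but are not the same. The article does not say that collectors come from outside the facility, stay away from the sessions, or are checked for unblinding.

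**Step 4: is there room for judgement?** By my reading of Tables 5 to 7, the fact-based items are drug type, duration of use, documented consent, next review date and taper. These are 5 of 9 antipsychotic indicators (3, 4, 5, 7, 8), 4 of 8 for benzodiazepines (3, 4, 6, 7) and 4 of 8 for antidepressants (3, 4, 6, 7), so 13 of 25. Others call for some judgement: whether non-drug strategies are tailored to the person (all three classes), or whether they were tried for long enough (benzodiazepine indicator 1).

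**Step 5: scale, for illustration only.** From Sample size and power: 19 facilities, 81% power at 5 points, more than 99% at 15 points. Neither alpha nor a standard deviation is stated, so I assume two-sided alpha 0.05 and a normal approximation. The plan's power cannot be reproduced independently; it can only be inverted.

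- Implied standard error of a strategy contrast: 5 / (1.960 + 0.878) = 1.76 points.
- Implied residual standard deviation: 1.76 / √(2/19) = 5.4 points.
- Consistency check: at 15 points, 15/1.76 − 1.96 is about 6.6, so power exceeds 99.9%. The two stated powers agree with each other.
- False-positive rate with no true effect and a spurious shift b: P(|Z + b/1.76| > 1.96).

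| Shift b (points) | b / 1.76 | False-positive rate |
|---|---|---|
| 0 | 0 | 5% |
| 1 | 0.57 | 9% |
| 2 | 1.14 | 21% |
| 3 | 1.70 | 40% |
| 5 | 2.84 | 81% |

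To show what such a shift would take: if 5% of truly non-concordant users in the Level 3 class were scored concordant (again an assumption), the shift would be 0.05 × (1 − true concordance). That is 4, 3 or 2 points at true concordance of 20%, 40% or 60%.

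**The case against.** The best case for the plan concerns the collectors. A reader might infer that they cannot be blind. The article does not support that. It places collectors at provider level, lets them be contracted, and does not say that they work in the facility they audit. A contracted or off-site collector could remain unaware, and separation rules may be in the full protocol. This stands, and it limits the collector point to blinding that is claimed but not shown to be protected.

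Other tempting routes to unblinding also fail.

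- Posters and letters announce that a broker service exists. Every facility has one, so they do not reveal the Level 3 class.
- Nothing says that the broker's work is written into progress notes or behaviour support plans.
- Factsheets reveal nothing, because every class gets them in every facility.
- Action plans go to facility management and the Medication Advisory Committee. Management is not among those described as blinded, so this matters only if a collector is present.

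The room for judgement is also limited. About half of the indicators are matters of fact, and the rule for combining them is in an additional file that is not shown. If several indicators must be met together, leaning on one would often not change a resident's status. Against the planned Level 3 effect of 15 points over Level 1, a 3-point shift is one fifth (3/15). A reader might take the 40% as a forecast of error; it is only what follows if a 3-point shift occurs.

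For staff, the label of partial disclosure does not help. The sentence still says that they are blinded to group, and the sessions disclose it.

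**Conclusion.** The point holds in two parts of different strength. For nurses and care workers who attend the sessions, the stated blinding is inconsistent with delivery; this follows from Table 1 and the session audience alone. For outcome collectors, blinding is asserted but not secured, because the collector pool overlaps that audience and nothing in the article separates them.

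Any scoring lean towards the Level 3 class would go straight into the within-facility contrast. Whether there would be one, and how large, cannot be known from the article. False-positive rates of about 9% to 81% for shifts of 1 to 5 points rest on an assumed alpha of 0.05, a standard error taken from the stated power for Level 2 against Level 1, and shifts chosen for illustration. They show that, if the contrast is as precise as the power claim implies, small differences in scoring matter. They do not show that the result will be biased.

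**What to change.** 1. Stop describing facility staff who attend the sessions as blinded. Say that they know the strategies and can infer the group.
2. Require that no collector audits a facility where they work, or where they attend education sessions, action-plan presentations or dashboard reviews. Use the providers' existing collectors. Where a provider cannot arrange this, for example because it has only one trained collector, report its outcome assessment as unblinded.
3. At 6 months, have each collector record a guess of the strategy for each class, and report the agreement with the true allocation.
4. Report the 6-month strategy contrast on the fact-based indicators (drug type, duration, consent, review date, taper) as a sensitivity analysis. Each indicator is already a secondary outcome at 6 months, so this needs no new data. Drug type applies to antipsychotics only, so the set differs slightly by class.

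The cost is a change of wording, some scheduling within each provider, and one extra question on the form. Providers with few collectors or widely separated facilities may find the second step hard, which is why it carries a reporting alternative.
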